**Step 3: Phone calls follow up: (15 minutes)**

The study team will contact both groups twice weekly and take a brief diet evaluation to assess the AGE content of their diet and compliance with the protocol.

**Step 4: final evaluation:**

Visit: This visit will take place one month after the first visit (enrollment and randomization visit). This visit will be scheduled to take place during the regular monthly dialysis visit, and the study blood samples will be obtained in addition to the blood samples obtained in the regular monthly visit

Diet evaluation: Candidates will bring detailed, accurate 3 days diet log for the nutritionist to evaluate.

Sample collection: Stool sample will be obtained and immediately stored in -80C at Annenberg building, floor 23 [name] lab. A total of 45 ml (three tablespoons) will be obtained during this visit. 15 ml (one tablespoon) will be sent to the hospital laboratory to evaluate dialysis parameters as the standard of care. An extra blood sample [30 ml (two tablespoons)] will be obtained for the research study. Blood will be centrifuged to separate supernatant and mononuclear cells and both fractions will be immediately stored in -80C at Annenberg building, floor 23 [name] lab. 24 hour urine samples will be obtained during this meeting and immediately stored in -80C at Annenberg building, floor 23 [name] lab.

Skin AGE measurement: Measurement of AGE levels in the skin will be done using an AGE reader. This AGE reader provides a non-invasive cardiovascular risk assessment by illuminating the skin of the forearm. The skin AGEs will emit a light that is detected by the AGE reader. The test will last about 10 seconds.

The expected duration of enrollment is **1** year.

The estimated date for the investigators to complete this study is 12/31/2016

- 1. Study Endpoints

Primary Endpoint: Change of gut microbiota after intervention.

Secondary Endpoint: Inflammatory and metabolic marker changes after intervention.

Safety endpoint: Candidates will be asked to either continue with their regular diet, or asked to cook their food in a different way, mainly boiling instead of frying/grilling. All cooking methods and measures to decrease AGE in diet are considered universally safe and are routinely recommended to the general population regardless of their medical conditions.

- 1. Procedures Involved in the Human Research

An initial phone interview will be conducted to invite potential study candidates to participate.

Face-to-face interviews will be performed to obtain consent and medical history as well as and provide training on recording dietary log. Stool, urine and blood samples will be obtained during both meetings.

Serum samples will be tested for levels of AGEs, IL-2, CRP, IL-10, creatinine, blood urea nitrogen, p-cresol, indoxyl sulfate, vitamin D and a global metabolite panel (the latter will be analyzed by non-targeted metabolite profiling platform combining ultrahigh performance liquid chromatography-tandem mass spectrometry optimized for basic species, optimized for acidic species, and gas chromatography/mass spectrometry). This metabolomic analysis will be performed by a third party (Metabolon). De-identified sample of one ml of serum will be sent to Metabolon® for metabolomic analysis.

AGE content, IL-2, CRP, IL-10, creatinine, blood urea nitrogen, p-cresol, indoxyl sulfate and vitamin D analysis will be done in [name] lab using ELISA, HPLC and other laboratory techniques as appropriate.

Metabolites in the urine will be analyzed by non-targeted metabolite profiling platform (the standard technique for metabolomic analysis). Urine will also be tested for AGEs,p-cresol, indoxyl sulfate using HPLC in [name] lab.

Stool will be used for comparisons of gut microbial composition by sequencing and comparing the V4 region of the 16S rRNA gene of bacterial DNA extracted from stool samples (De-identified samples will be sent to [name] lab, Mount Sinai Genetics and Genomic Sciences).

Measurement of AGE levels in the skin will be done using an AGE reader. This AGE reader provides a non-invasive cardiovascular risk assessment by illuminating the skin of the forearm. The skin AGEs will emit a light that is detected by the AGE reader. The test will last about 10 seconds.

At investigator’s lab blood will be centrifuged for separation of supernatant from peripheral mononuclear cells (PMNC). Supernatant will be tested for the AGEs: carboxymethyllysine (CML), methylglyoxal (MG), 8-isoprostane, insulin, leptin, and adiponectin. PMNC protein will be used to asses TNF-a, and intracellular AGEs. PMNC mRNA will be used to asses AGER1, RAGE and SIRT-1.

- 1. Specimen Banking

All samples (serum, urine and stool) will be stored and banked in the Annenberg building 23rd floor, in -80 degree C temperature freezer. Samples will be stored until the study is concluded (estimate date 12/31/2016). Designated study person by PI will have access to the area where specimens are stored.

Samples will be given a unique letter code and no health protected information will be used in labeling the samples (As explained in details below in paragraph “h”).

Metabolon Inc. Durham NC. (Company responsible of metabolite analysis) will receive specimens labeled with the letter code. No protected health information will be submitted with the specimens. Regulatory agency will be permitted access the results of these analyses upon request. All requests will have to be approved by the study principle investigator.

Stool samples for microbiota study will be handled by [name] lab.

- 1. Data Management and Confidentiality

Names and dates of birth will be stored in a file, and each patient will be assigned a letter code. Data collected will be stored in a separate file, using the assigned letter code as the identifier. Both files will be stored in a computerized database with a secure access and password available only to the investigators.

After initial processing of samples, a small portion of serum, stool and urine will be sent completely de-identified to Metabolon Inc. Durham NC. for metabolite analysis.

The results of their serum samples or urine samples will not be shared with the patients. No subject identifiers will be shared with Metabolon Inc. All data used in this study will be de-identified before being transferred to any person, organization, or database outside of Mount Sinai Medical Center. All patients will only be identified by the letter code (As mentioned above) on all study related materials in patient research folders and on the database. The log linking ID numbers to patient identities will be kept in a password protected and encrypted file on a Mount Sinai networked computer. The data will be kept for at least 2 years after the completion of the study. When transmitting data, only de- identified data will be used. All identifiable patient information will be stored on Mount Sinai’s protected server. All paper copies of forms and patient health information will be stored in a locked room at Mount Sinai Hospital.

Data will be analyzed using SPSS statistical program, for categorical values chi-square test will be used, for non categorical values analysis of variance (ANOVA) will be used.

Gut microbiota will be analyzed by sequencing of V4 region of 16S rRNA. Sequencing data will be analyzed using Qiime program ([name] lab).

- 1. Provisions to Monitor the Data to Ensure the Safety of subjects

**Part I** describes the safety monitoring activities that will be undertaken in during the study. This should be completed for all studies that require more than the basic minimum DSMP.

**Part II** describes Data and Safety Monitoring Committees or Boards and should be completed when one is needed for the DSMP

**Part III** describes requests for alteration of some or all of the reporting requirements for adverse events. This may be part of a larger DSMP but may also be completed by investigators using the basic minimum DSMP as described in the Data and Safety Monitoring Guidance.

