- It is thought that certain dietary AGEs are largely undigested by human gut enzymes and eventually enter the colon, where they may act as a growth substrate for detrimental bacteria such as some Clostridium and Bacteroides species . Therefore it is conceivable that individuals who consume highly processed diets (which contain large quantities of AGEs) may adversely alter their colonic microbial composition, potentially enhancing their risk for the development of metabolic diseases such as obesity and type 2 diabetes .
- The purpose of this study is to find out if a diet low in Advanced Glycation End product (Low-AGE diet) can improve the composition and diversity of gut bacteria in patients with ESRD on PD.

1. Setting of the Human Research

This is a pilot study. All research procedures will be performed at Icahn School of Medicine at Mount Sinai. Potential study participants will be evaluated at Peritoneal Dialysis Unit:

Entrance:       [name]

(Klingenstein Clinical Center (KCC) Building)

Peritoneal Dialysis Unit (PDU): Annenberg Building, MC level, room 403 (Nursing Station)

[contact]

*Patients with ESRD receiving PD at Icahn School of Medicine at Mount Sinai will be invited by their primary care nephrologist ([name]) to participate in the study.*

No involvement of any community advisory board for research conducted outside of MSSM.

1. Resources Available to Conduct the Human Research

We have a clinical research team made up of [name], PI; [name], Co-Investigator; [name], Co-Investigator; [name], Co-Investigator; [name], Senior Clinical Research Coordinator; and Dietitian, [name], RD, CDE.

At the beginning of this study, Standard Operating Procedure (SOP) will be established to ensure that all individuals involved in the study know the study procedures. Each member of the team will be adequately informed about the protocol, the investigational plans in reference to the AGE diet and their trial-related duties and functions.

1. Study Design
   1. Recruitment Methods

Potential participants will be identified and recruited from the Peritoneal Dialysis Unit. Patients with ESRD on PD and receiving treatment at Mount Sinai Hospital will be identified from the PD patient list.

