**Step 1: Candidates identification:**

Invitation: All patients with ESRD on PD in the peritoneal dialysis unit will receive a letter of invitation and diet log sheet (forms attached).

Phone call 1 (15-30 minutes): Two weeks after sending the letters of invitation, the study team will contact the candidates and invite them to participate in the study. The investigators will explain in detail the hypothesis and objectives of the study, the methods of obtaining a dietary log and will answer all questions asked by the candidate. No HPI will be obtained in this phone call.

A screening and consent signing visit will be scheduled within 2 weeks after the phone call.

HIPPA waiver authorization to identify and contact the candidates is submitted (see attached).

Step 2: Screening and consent visit:

A face-to-face interview (60 minutes): This interview will be held within 1-2 weeks after “phone call 1.” During this interview, a detailed review of the study design, methods and goal will be provided and explained to the candidates. If the subject agrees to participate in the study, and to ensure compliance with HIPPA regulation, he/she will be asked to read/sign the consent form before obtaining any HPI. Signing the consent form does not mean that the subject is enrolled in the study. After signing the consent form, eligibility screen will be conducted and the subject will be enrolled in the study if eligible.

A review of medical history and medication to evaluate for eligibility will take place after signing the consent form.

Candidates will provide the dietary log and discuss it with the interviewer.

Candidates will be given consenting review/survey document (see attached) to answer to ensure full understanding of the study and acceptance to participate. All candidates will be provided with the appropriate tools to obtain the stool and urine samples (disposable: two ice packs, a box, two tubes, and 24 hour urine collection container).

Dietary evaluation: A dietitian will review the de-identified diet log and estimate the daily AGEs consumption.

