**Step 2: first visit:**

Enrollment: At this point, candidates are officially enrolled in the study. . Patients on PD are seen by their primary nephrologist every month and blood tests are obtained monthly to evaluate dialysis efficacy and other parameters in this population (standard treatment for ESRD patients on PD).

The first visit will be scheduled to take place during one of the regular monthly dialysis visit, and the study blood samples will be obtained in addition to the blood samples obtained in the regular monthly visit.

Medical evaluation: This will take place during the PD monthly visit. Vital sign measurements and physical examination will be conducted as part of the standard of care, and reviewed by the investigators.

Diet evaluation: Candidates will bring detailed, accurate 3 day diet log for the nutritionist to evaluate.

Sample collection: Stool sample will be obtained and immediately stored in -80C at Annenberg building, floor 23 [name] lab. A total of 45 ml (three tablespoons) will be obtained during this visit. 15 ml (one tablespoon) will be sent to the hospital laboratory to evaluate dialysis parameters as the standard of care. An extra blood sample [30 ml (two tablespoons)] will be obtained for the research study. Blood will be centrifuged to separate supernatant and mononuclear cells and both fractions will be immediately stored in -80C at Annenberg building, floor 23 ([name] lab). 24 hour urine samples will be obtained during this meeting and immediately stored at -80C at Annenberg building, floor 23 [name] lab (see paragraph f for details). Candidates will be given another set of sample collection tools (disposable: two ice packs, a box, two tubes, and urine collection container) to bring in the second visit.

Skin AGE measurement: Measurement of AGE levels in the skin will be done using an AGE reader. This AGE reader provides a non-invasive cardiovascular risk assessment by illuminating the skin of the forearm. The skin AGEs will emit a light that is detected by the AGE reader. The test will last about 10 seconds.

Randomization: Candidates will be randomly assigned to either continue the same diet [G1], or switch to low AGE diet [G2].

Diet education (30 minutes): The study dietitian will meet with both groups and instruct them in regards to food preparation and its content of AGE. Handouts will be given to both groups (see attached).

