**MSSM Additional Monitor:**

Check One: PI:  Team Member:  Independent:

Last Name: [name]

First Name: [name]

Academic Title: Professor of Medicine

Department: Medicine

Mailing Address: MSSM, [name],

[name]

[contact]

[contact]

E-mail: [contact]

Drs. [name] and [name] will be responsible for data and safety monitoring for this study on a daily basis. [name] will perform an independent monitoring in our study every three months.

2. Justify your choice of principal monitor in terms of the assessed risk to the research subject‘s health and wellbeing. In high risk studies when the principal monitor is independent of the study staff, indicate the individual’s credentials, relationship to the PI, and the rationale for selection.

This is an open-label, low-risk dietary intervention involving adult subjects with peritoneal dialysis, in a single clinical site over a period of about 1 month, and with one research team. Therefore, an independent DSMB is not warranted. Drs. [name] and [name] will be evaluating each and all of these patients on a regular basis to determine any potential adverse events. [name] will monitor independently the study, and will start after the enrollment of the first five participants and every 3 months onwards.

3. List the specific items that will be monitored for safety (e.g., adverse events, subject compliance with the protocol, drop outs, etc.).

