***Safety monitoring***

*The following elements will be monitored:*

- *Serious and unanticipated adverse events*
- *The totality of adverse events including expected and less than serious*
- *Reasons for subjects withdrawing from the study*
- *Changes in nutritional parameters from baseline*
- *Changes in concomitant medications*

4. Indicate the frequency at which **ACCUMULATED** safety and data information (items listed in number 3 above and interim analysis of efficacy outcomes) will be reviewed by the monitor(s) or the Data Monitoring Committee (DMC). Although this information must be reviewed at least annually, the higher the study risks, the more frequently reviews must be scheduled.

Monitoring will take place at every visit or following any serious adverse event until the completion of the study. Cumulative safety and data monitoring will be reviewed semiannually. Independent monitor will review cumulative data and safety semiannually.

Semiannually we will create a summary of safety to be reviewed by the Independent Monitor, [name], and to be sent to the MSSM IRB with an annual progress report.

5. Where applicable, describe rules which will guide interruption or alteration of the study design.

Participation of a person will be terminated in cases of noncompliance with study diet and design.The participation of candidates who fail to answer the follow up phone calls for 2 consecutive weeks, or report the nonadherence to diet for more than one week will be terminated.

6. Where applicable, indicate dose selection procedures that will be used to minimize toxicity.

N/A. This is a dietary intervention. No dose selection is possible.

7. List any specialized grading system that will be used to evaluate adverse events (e.g., National Cancer Institute Common Toxicity Criteria).

N/A.

8. Describe procedures that will be used to assure data accuracy and completeness.

This is a study involving a small number of subjects for about 1-month period by an experienced research team (Dr. [name], [name], [name], research coordinator(s) and study dietitian(s)), which will pay personal attention to each participant.

9. Should a temporary or permanent suspension of your study occur, in addition to the PPHS, to whom (NIH, FDA, sponsor, IRB) will you report the occurrence?

Any such situation will be immediately reported to the IRB, and PDU.

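### The final diet log, the only full direct record of AGE intake after randomisation, is scored with no masking to arm in an open-label trial, probably by the dietitian who taught the diet.

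*Protocol*

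**What the plan says.** The monitoring plan (Part I, item 2) describes the trial: "This is an open-label, low-risk dietary intervention involving adult subjects with peritoneal dialysis, in a single clinical site". Group 1 continues its usual diet and group 2 is told to start a low-AGE diet. The change is mainly one of cooking method, with boiling replacing frying and grilling (Study Endpoints, safety endpoint).

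Dietary intake is recorded at these points around and after randomisation:

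- **First visit, diet evaluation:** "Candidates will bring detailed, accurate 3 day diet log for the nutritionist to evaluate". This is listed before randomisation in the visit sequence.
- **First visit, diet education, listed after randomisation:** "The study dietitian will meet with both groups and instruct them in regards to food preparation and its content of AGE".
- **Follow-up:** twice-weekly phone calls with a short check of diet and compliance.
- **Final visit, one month later:** "Candidates will bring detailed, accurate 3 days diet log for the nutritionist to evaluate".

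The section on resources lists a single dietitian, "Dietitian, [name], RD, CDE", and no separate nutritionist. The monitoring plan elsewhere allows for more than one dietitian. No sentence says that whoever scores the final log is unaware of the participant's group.

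**The concern.** Scoring AGE intake from a food record takes judgement on how a food was cooked and how much was eaten. Here cooking method is the very thing the intervention changes. A scorer who knows the group, and who may have taught the diet, can settle an unclear entry in the direction expected for that group. No bad faith is needed.

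The intake contrast matters because it tells a reader whether the diet was delivered. If a null microbiota result comes with good separation, it counts against the hypothesis. If it comes with little separation, it says little. If microbiota changes and the separation is exaggerated, crediting the change to lower AGE intake looks better supported than it is. The protocol plans for at least 10 participants per group at study end, so either reading will lean on supporting evidence of this kind.

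**Working it through.** The protocol has no figure to reproduce. The check sets its statements side by side.

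1. **Is the arm known?** Yes. The monitoring plan calls the trial open-label.

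2. **What measures intake after randomisation?** The calls are brief, so the final 3-day log is the only full dietary record.

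3. **Do other measures replace it?** Serum AGEs (including CML and MG), urine AGEs, intracellular AGEs and a skin reading are planned, and the dietitian has no part in scoring them. They do not isolate intake. The Background says AGEs also form in the body, more so under oxidative stress such as in ESRD. The second research question treats serum AGEs as something the microbiota change may alter, so as an outcome. The protocol does not name any of these measures as a check on dietary exposure.

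4. **Who scores the log?** A nutritionist, by title. With one dietitian listed and that role also teaching the diet, the scorer is probably the teacher. This is an inference.

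5. **Which log is exposed?** As listed, the first-visit log is evaluated before an arm exists. The final log is evaluated when the arm is known. The final log therefore carries the risk. The first-visit log belongs in the fix so that both halves of the change are scored in the same way.

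6. **What can be biased?** The intake contrast. The primary endpoint is bacterial gene sequencing on de-identified stool, and the secondary markers are laboratory assays. Log scoring enters none of these.

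7. **How large could it be?** A calculation would need the spread of AGE intake, the expected difference between groups and the share of unclear log entries. The protocol gives none of them. Its only intake figure is the entry threshold of more than 12 AGE Eq/day, which says nothing about scoring error.

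8. **How much work is the fix?** 30 participants × 2 logs = 60 logs at full enrolment. If 10 per group finish, 20 × 2 = 40 logs form complete pairs.

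**The case against.** Dietary intake is not a named endpoint, and no rule ties the reading of the primary result to it. The protocol promises a standard operating procedure for study procedures, which may settle who scores the logs. Recorded cooking methods will often give the arm away. Masked scoring also does nothing about participants who report what they were taught. The protocol adds to that pressure, because reporting non-adherence for more than one week ends participation. Late scoring would also keep scored intake out of the weekly meeting's review.

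Most of this stands, and it limits the weight of the point. It does not remove it. Who scores a log, and knowing what, is trial conduct that has to be fixed before scoring starts, and the protocol is silent. The delay costs little for trial conduct: eligibility rests on the screening log, the final log arrives when follow-up ends, and the calls handle adherence meanwhile.

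A reader might infer three stronger points that the text does not support:

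- **That the protocol masks one log and not another.** At screening, "A dietitian will review the de-identified diet log and estimate the daily AGEs consumption". No arm exists then, so this hides identity and not allocation. The participant also talks the log through: "Candidates will provide the dietary log and discuss it with the interviewer". It is not an allocation-masking rule that was later dropped.
- **That a before-after change mixes a masked and an unmasked reading.** The natural baseline is the first-visit log, collected in almost the same terms as the final one. Nothing makes the screening log the baseline.
- **That the log is scored face to face by the person who taught the diet.** The log is brought to the visit, but face-to-face scoring is not stated. The protocol uses two titles and in places allows several dietitians.

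**Conclusion.** The point holds as a modest weakness in conduct that is worth correcting. The main record of dietary separation is self-reported and is read with no stated masking, probably by someone who knows the group. The primary endpoint is not biased. At risk is the estimated intake difference and the interpretation built on it. The likely direction is an exaggerated separation, but its size cannot be calculated from the protocol.

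This rests on two assumptions. One is that the nutritionist and the listed dietitian are the same person, or at least that the nutritionist knows the arm. The other is that the log will be used to judge whether the diets differed, which the protocol implies by collecting it but does not state.

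**What to change.** Amend the diet evaluation text for the first and final visits:

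- File both logs under the letter code already set out under Data Management and Confidentiality, with arm, visit and dates removed. The coordinator keeps the key that links each log to its visit.
- At the visit, check only that the log is complete, with cooking method and portion filled in.
- After the last participant's final visit, have the same dietitian score all logs in random order, using one food table.
- Report the serum, urine and skin AGE measures beside the logs as supporting evidence of separation. They cannot confirm it, for the reasons in step 3 of the working.

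The cost is a wording change and some filing. It needs no new staff, samples, visits or burden on participants. Intake scores arrive later, possibly by most of the 12-month enrolment period for the earliest participants. Masking is partial, since cooking methods can reveal the arm and a dietitian in a small trial may recognise a log. Participants' own reporting bias is untouched and should be stated as a limitation.

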**Brief Summary of Research (250-400 words):**

Gut microbes can influence numerous aspects of human biology. Alterations in the function and composition of gut microbial flora (gut microbiota) have been linked to inflammatory bowel disease, chronic inflammation, dyslipidemia, diabetes mellitus, atopic disorders, cardiovascular disease, neoplasms, and obesity. Diet and other environmental factors have been found to alter the gut microbiome, and recent studies have shown that gut microbiota is altered in patients with end stage renal disease (ESRD) who are receiving renal replacement therapy (hemodialysis). However, little is known on whether the alteration in gut microbiota seen in renal patients is due to uremia. Several lines of evidence suggest that renal failure alters the chemical environment of the intestinal lumen which could impose a selective pressure on the growth of certain gut microbes, or is an epiphenomenal finding due to the complex confounding factors. This alteration in the gut microbiota of patients with renal failure significantly impacts the development of co-morbid conditions such as accelerated atherosclerosis, abnormal bone mineral metabolism, and chronic inflammation that are associated with renal failure. We hypothesize that the gut microbiota of patients with ESRD is highly diet dependant, and that changing the diet to a low advanced glycation end products (AGEs) diet will result in a better microbial composition and characteristics in the gut of patients with ESRD on peritoneal dialysis (PD).

1. Objectives:

*Research Question:*

- 1. How does a diet low or high in Advanced Glycation End products (AGEs) change the composition and activity of gut microbiota in patients with ESRD on PD?
  2. Will these changes in gut microbiota affect the serum levels of AGEs along with other inflammatory markers?
  3. Can a diet low in AGEs be associated with improvement in gut microbiota and therefore improve markers of chronic inflammation in ESRD patient?

The purpose of this study is to find out if a diet low in Advanced Glycation End products (Low-AGE diet) can improve the composition and diversity of gut bacteria in people with ESRD on PD.

1. Background

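### The primary endpoint names no single 16S-derived variable, no criterion of improvement and no between-arm contrast, so the primary result could be chosen after the data are seen

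*Protocol*

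**What the plan says.** Study Endpoints gives the primary outcome in one phrase: "Primary Endpoint: Change of gut microbiota after intervention". Other sections touch on it as follows.

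- **Aims.** The research question asks how diet will "change the composition and activity of gut microbiota in patients with ESRD on PD". The purpose is to learn whether the diet "can improve the composition and diversity of gut bacteria in people with ESRD on PD". The hypothesis is that it "will result in a better microbial composition and characteristics in the gut of patients with ESRD".
- **Background.** CKD is linked to fewer saccharolytic bacteria (Lactobacillaceae and Prevotellaceae). Undigested dietary AGEs may be a "growth substrate for detrimental bacteria such as some Clostridium and Bacteroides species".
- **Assay.** Procedures Involved in the Human Research says stool will be used for "comparisons of gut microbial composition by sequencing and comparing the V4 region of the 16S rRNA gene".
- **Analysis.** Data Management and Confidentiality has a general sentence naming SPSS, with chi-square for categorical values, and "for non categorical values analysis of variance (ANOVA) will be used". A separate sentence assigns the sequencing data to Qiime. It names no output, test or comparison.
- **Design.** Participants are randomised to keep their diet (G1) or switch to a low-AGE diet (G2). Both arms give stool at the first visit and one month later. Number of Subjects plans 15 per arm, expects at least 10 per arm at the end, calls the study a pilot and states that power could not be calculated.

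**The concern.** A primary endpoint should let a reader decide, before any data exist, what result would count as meeting it. That needs a variable, a favourable direction and a comparison, and this one fixes none of them.

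16S sequencing does not give one number per patient. It gives several diversity indices, several between-sample distances and many taxa, and these need not move together. If none is designated, whichever shows a difference can be reported as the primary finding. With improvement undefined, a shift either way could be presented as favourable.

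The contrast is open too. Wording that refers to change after the intervention also fits a before-after comparison within G2. That would discard the randomised control and absorb time effects, together with the effects of dietitian contact and twice-weekly calls, which both arms receive. The study is open-label, which makes fixing these choices in advance more important.

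**Working it through.** **No stated figure to reproduce.** The protocol gives no alpha, power, effect size or SD. The check is therefore a reading of the text, followed by an illustration of what the open choices cost.

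**Step 1. Is the endpoint completed elsewhere?**

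| Element needed | What the protocol supplies | Fixed? |
| --- | --- | --- |
| Variable | Assay (16S V4) and software (Qiime). The aims pair composition with activity, with diversity and with characteristics, which are different quantities | No |
| Favourable direction | Improvement is claimed in the purpose and hypothesis; some taxa are described in the Background | Loosely stated, not made a criterion |
| Contrast | Two randomised arms, stool at both visits | Implied by the design, not stated for the endpoint or in the analysis sentences |
| Time | Final visit one month after the first | Yes |

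**Step 2. Cost of leaving the measure open.** Assumptions, none of them from the protocol: two-sided 5% per test, no diet effect, and k candidate measures. For independent measures the chance of at least one false positive is 1 − 0.95^k:

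- k = 1: 5%
- k = 5: 1 − 0.95^5 = 22.6%
- k = 10: 1 − 0.95^10 = 40.1%
- k = 20: 1 − 0.95^20 = 64.2%

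Microbiota measures from one stool sample are correlated, so independence overstates the problem. A simulation of k equally correlated normal measures (10 per arm, the protocol's minimum number of completers; two-sample t-tests; 20,000 replicates) gives:

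| k | Independent | Correlation 0.5 | Correlation 0.8 |
| --- | --- | --- | --- |
| 2 | 9.8% | 9.0% | 8.2% |
| 5 | 22.6% | 18.7% | 13.4% |
| 10 | 40.1% | 29.5% | 18.2% |
| 20 | 64.2% | 43.3% | 23.4% |

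**Step 3. Cost of leaving only the contrast open.** Take one measure and three possible tests: before-after within G2, G2 versus G1 on change, and G2 versus G1 at follow-up. With 10 per arm, no diet effect, no time effect and 40,000 replicates, the chance that at least one is significant is 12.4% at a baseline-to-follow-up correlation of 0.5 and 12.7% at 0.7. A time effect shared by both arms would raise this, because the within-G2 test would detect it.

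**Step 4. After the fix.** With one named measure and one contrast, the chance of a false primary finding is the assumed 5%.

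**The case against.** The strongest reply has three parts.

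1. **The design already points to the answer.** Randomisation, a usual-diet control arm, stool from both arms at both visits and a research question about low and high AGE diets all suggest G2 versus G1. No section plans an analysis of G2 alone. This stands as an account of intent, but neither the endpoint nor the analysis sentences say so.
2. **A direction is not wholly absent.** The purpose speaks of improving composition and diversity, and the Background names taxa on each side. This stands too. The fair criticism is that the direction is not carried into the endpoint.
3. **This is a pilot, and an analysis plan may exist.** No confirmatory claim or power is stated, which lowers the severity. Distance metrics, Qiime settings, model terms and false-discovery control can properly wait for a plan. The identity of the primary variable and its comparison is protocol content. A pilot is also a natural source of the effect size and SD for a later trial, and here it is undefined which estimate to carry forward.

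A reader might infer stronger claims that the document does not support:

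- **That ANOVA will be run on community composition or taxon by taxon.** The ANOVA sentence is general, and the sequencing data are handled in a separate sentence under Qiime.
- **That regression to the mean distorts the primary endpoint.** Entry selects on high AGE intake, not on a microbiota measure, so any such effect is indirect.
- **That a false positive is nearly certain.** Fifty or 100 independent taxa at 5% would give 92% or 99%. However, the number of taxa, their independence and the 5% level are all assumed, and no rule says that one significant taxon counts as success.
- **That the secondary endpoint, "Secondary Endpoint: Inflammatory and metabolic marker changes after intervention", is defective for the same reason.** Ranking those markers and controlling error among them can be left to an analysis plan.

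**Conclusion.** The point holds. As written, the primary endpoint cannot be said to be met or not met: its variable and contrast are not stated, and its direction appears only as general aims. The conclusion rests on the text and needs no numerical assumption.

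The size is illustrative. With 10 candidate measures, the chance of at least one false positive is about 40% if they are independent, 30% at correlation 0.5 and 18% at 0.8. With the contrast alone open it is about 12-13%. The comparison value is 5%. These figures assume 5% per test, the stated number of measures, equal correlations and, for the contrast, no time effect. Pilot status makes this something that should be fixed; it does not invalidate the study.

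**What to change.** Reword the primary endpoint to contain three things:

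- **One 16S-derived variable with its favourable direction.** Shannon diversity, with higher values favourable, would suit the stated purpose. One named community-composition measure would suit the hypothesis. Either is defensible, provided one is chosen in advance and the criterion for improvement is stated.
- **The contrast.** G2 versus G1 at one month, adjusted for the first-visit value.
- **The status of everything else.** Label all other microbiota results secondary or exploratory.

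The cost is protocol wording. The baseline and one-month stool samples are already planned from both arms, so no new visits, samples or participants are needed. The downside is that fewer results can be presented as primary.
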